### Interim analyses {21b}

N/A. No interim analyses are planned.

### Methods for additional analyses (e.g., subgroup analyses) {20b}

The difference in percentages between the two groups will be determined by a chi-square test, thus allowing the main objective to be met. This result will be adjusted according to several criteria, in particular two of them: a center effect, a baseline effect, and an effect of the degree of experience of the nurse.

Indeed, the analysis of cluster trials is more complex than the analysis of trials with individual randomization units. The analysis will therefore also be performed at the cluster level using the Health French Authority of June 2007 cluster (methodological guide downloadable from www.has-sante.fr).

### Methods in analysis to handle protocol non-adherence and any statistical methods to handle missing data {20c}

For missing data, if less than 5% of the sample contains at least one missing data point, it will not be imputed. The analysis will be performed as a complete case analysis. If more than 5% of the sample contains at least one missing data point, there are two options. If a variable contains less than 20% of missing data, we perform multiple imputation by chained equations (MICE). If a variable contains more than 20% missing data, it cannot be introduced in a statistical model.

### Plans to give access to the full protocol, participant-level data and statistical code {31c}

There are no plans for granting public access to the full protocol, participant-level data, and statistical code.

The datasets analyzed during the current study and statistical code are available from the corresponding author on reasonable request, as is the full protocol.

## Oversight and monitoring

### Composition of the coordinating center and trial steering committee {5d}

No trial steering committee is defined in the protocol. The coordinating investigator and sponsor project manager provide day-to-day management of the trial. There is no Stakeholder and Public Involvement Group (SPIG).

### Composition of the data monitoring committee, its role and reporting structure {21a}

The medical procedures used in this trial comply with the most recent recommendations of the Declaration of Helsinki and French Public Health Law 2004–806 of August 9, 2004, on subject protection and safety in accordance with good clinical practice. A person mandated by the sponsor will ensure monitoring of this trial to guarantee that accurate, full, and reliable data are collected. The level of monitoring will be adapted to the low risk of the study.

At the end of the study, the data review committee, comprising the data manager, the biostatistician, and an independent dermatologist, will review all deviations from the protocol. Other members may join the committee to provide some details on the context of each deviation. The committee will qualify deviations as major or minor and shall clarify the relevance of the data with respect to these deviations: conservation of the data (for minor deviation) or exclusion of the data (for major deviation). Major deviations can affect subject safety or rights. Additionally, by definition, the intention-to-treat analysis requires that all data be kept for the analysis, even major deviations, except in the event of absence or withdrawal of written consent that systematically results in the exclusion of any data on the research.

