#### Second phase: simulation-based training

The training at the next center starts at the end of the training of the previous center (duration per center: approximately 2 months).

The simulation-based training program is based on the pedagogical strategies described in simulation and seems to be relevant in this context, i.e., deliberate practice, mastery learning, and rapid cycle deliberate practice.

Peyton’s “4 steps” method is used for new learning. We will propose a variation of this learning tool that is more adapted for a group.

A “minimum passing score” (MPS) will be established on the main steps necessary to perform the procedure, including respect for good hygiene practices and effective communication. If the MPS is not reached, the learner can repeat the different workshops until an acceptable score is obtained (90% of correct answers).

The training will take place on a procedural mannequin, that is, an arm with a pulsatile AVF that is echogenic.

The training also includes a scenario with simulated patients using the “rapid cycle deliberate practice” method [19]. It is relevant to work on communication with the patient during procedural simulation.

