## Assignment of interventions: blinding

### Who will be blinded {17a}

N/A. Blinding is not possible in this study.

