## Data collection and management

### Plans for assessment and collection of outcomes {18a}

Data will be managed in a database administered by the sponsor. Data entry will be performed by the investigators at each center and may be performed by any person on the task delegation list. The system used for the computerized database will be in accordance with the regulations in force, particularly MR-01. Access to the database will be limited to authorized persons only (sponsor team, investigation team, principal investigator), and rights (read, write, specific pages of the case report form, patients of the center or all patients, etc.) will be assigned according to their role in the study and their center. Authentication of users will be assured by means of a username and a password personalized for each user. Connections to the database will be recorded in the connection history.

Consistency tests may be scheduled depending on the level of risk and/or impact of the study as defined by the sponsor. Following the execution of these tests, requests for clarification (queries) may be sent to the investigators to correct or confirm data entered in the database. Depending on the level of risk and/or impact of the study, a preanalysis committee may meet before the data are exported to qualify the deviations identified during the study and to decide whether or not to include the data collected in the study.

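### The article gives two opposing rules for data with a major deviation and does not say which one governs the primary comparison

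*Protocol article*

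**What the plan says.** Three parts of the protocol article bear on this point.

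- **Data monitoring committee {21a}.** At the end of the study a data review committee (data manager, biostatistician, an independent physician, others if needed) classes each deviation as major or minor. Data with a minor one stay; for a major one the stated consequence is "exclusion of the data (for major deviation". The paragraph closes by saying that "by definition, the intention-to-treat analysis requires that all data be kept for the analysis, even major deviations". Its one carve-out is for subjects who gave no written consent or took it back. The only content given for a major deviation is that it can affect subjects' safety or rights.
- **Assessment and collection of outcomes {18a}.** A pre-analysis committee may meet before data export to qualify deviations and "to decide whether or not to include the data collected in the study". Intention-to-treat is not mentioned there.
- **Statistical methods {20a}, {20b}, {20c}.** The primary comparison is a chi-square test with adjustments. No analysis population is named. The section whose heading covers protocol non-adherence contains only missing-data rules.

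On masking, section {17a} says "Blinding is not possible in this study". Nothing is said about whether the reviewing committee sees allocation or outcomes.

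**The concern.** A cluster-randomised comparison is protected only while every eligible puncture is counted under the arm to which its centre was allocated. Here one sentence removes data with major deviations and a later sentence keeps them. A second section grants the removal power again without the limit. Whoever runs the primary test can cite the text for either data set.

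That matters more than usual here. The trial is open-label, the classification is a judgement with almost no stated criteria, and the statistician sits on the committee. If exclusion is related to outcome and differs between arms, the primary result no longer estimates the effect of allocation. The arms also differ in how many steps a nurse must complete, so unequal deviation counts are conceivable.

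**Working it through.** **Step 1. Setting the rules side by side**

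| Place | Data with a major deviation | Exception | Applies to the primary test? |
|---|---|---|---|
| {21a}, committee's task | Excluded | None stated | Not stated |
| {21a}, closing sentence | Kept under intention-to-treat | Consent absent or withdrawn | Not stated |
| {18a} | Committee decides | None stated | Not stated |
| {20a}, {20b} | Silent | – | Chi-square test, no population named |
| {20c} | Silent (missing data only) | – | – |

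The rows can be reconciled only by adding two things: that the exclusion rule defines a secondary set, and that intention-to-treat is the primary set. The article says neither. Intention-to-treat is mentioned only in {21a}, and no per-protocol set is named anywhere. The rules conflict without being strictly impossible to satisfy together.

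**Step 2. Could exclusions be unequal?**

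Both arms take the same e-learning with a 90% pass mark; in the control arm the text sets a limit of 1 month. Only the simulation arm adds a one-day session and workshops with their own score, for which "If the MPS is not reached, the learner can repeat the different workshops until an acceptable score is obtained". That arm has more steps that can be missed. This shows that imbalance is possible. It does not show that it will occur, because no section makes missed training a major deviation.

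**Step 3. What a bias would look like**

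The plan has no figure of its own to reproduce here. Inputs taken from the sample size section {14} are an event rate of 9.3%, and 4.65% after the planned halving, so a planned effect of 9.3 − 4.65 = 4.65 points. The inputs I assume are:

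- no true effect, so 9.3% in both arms;
- exclusions in one arm only, covering a fraction f of its punctures;
- an event rate in the excluded punctures that is RR times the rate in those kept.

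Let k be the rate among punctures kept. Then 0.093 = (1 − f)·k + f·RR·k, so k = 0.093 / (1 − f + f·RR).

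| f | RR = 0.5 | RR = 1 | RR = 1.5 | RR = 2 |
|---|---|---|---|---|
| 5% | 0.093/0.975 = 9.54% (−0.24) | 9.3% (0) | 0.093/1.025 = 9.07% (0.23) | 0.093/1.05 = 8.86% (0.44) |
| 10% | 0.093/0.95 = 9.79% (−0.49) | 9.3% (0) | 0.093/1.05 = 8.86% (0.44) | 0.093/1.10 = 8.45% (0.85) |
| 20% | 0.093/0.90 = 10.33% (−1.03) | 9.3% (0) | 0.093/1.10 = 8.45% (0.85) | 0.093/1.20 = 7.75% (1.55) |

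Brackets give 9.3% minus k in percentage points. A positive value falsely favours the arm with exclusions. The largest entry is 1.55/4.65, one third of the planned effect. The sign depends wholly on RR, and the column RR = 1 shows no bias at any f. If both arms lost the same fraction at the same RR, both rates would fall equally and the difference would stay at zero.

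**The case against.** The strongest reply is that {21a} has an ordinary reading: exclusion describes a deviation-free set and the closing sentence describes intention-to-treat, which is the only analysis set the article names. Assigning sets to tests is commonly left to a statistical analysis plan, which is not shown. The first half is a fair reading, and silence in the statistical sections alone would not be a finding. But the article is not merely silent. It states an exclusion rule and its opposite, and repeats the power in {18a} without the limit.

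A reader might also infer four stronger things, which the documents do not support.

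- **That exclusions will fall mainly on the simulation arm.** Missed training or a low score is nowhere defined as a major deviation. A low workshop score leads to repetition. The control arm has its own pass mark, and all nurses are to be trained {11b}.
- **That punctures by weaker nurses will be removed, favouring simulation.** Nurse numbers are known only to the nurses themselves {27}, and no route is described for linking training scores to excluded punctures.
- **That the reviewers are unmasked.** The statement in {17a} answers who is blinded in the trial. It does not say what the committee sees, and {18a} places the decision before export. All that can be said is that no masking is stated.
- **That there are two committees, both acting at the end of the study.** Sections {18a} and {21a} give the same task and may describe one body.

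**Conclusion.** The point holds as an unresolved conflict in the rules for the analysis set. As written, deviation-based exclusions could enter the primary result, and the text does not prevent them from being decided with knowledge of arm or outcome. Whether this would bias the result, in which direction and by how much cannot be determined from the documents. That depends on exclusion being related to outcome and differing between arms. The range of −1.03 to 1.55 points in the working rests on assumed values of f and RR and on one-sided exclusion, so it is an illustration and not an estimate. The conflict should be settled before analysis because it touches the primary comparison, but it does not show that the result will be biased.

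**What to change.** 1. In the statistical methods {20a}, state that the primary analysis is intention-to-treat: all recorded eligible punctures, analysed under the centre's allocated arm, with absent or withdrawn consent as the only exclusion. This makes the sponsor's own closing sentence in {21a} govern.
2. In {18a} and {21a}, limit exclusion for major deviations to a named secondary (per-protocol) analysis. The committee's review role can stay.
3. Have deviations classified before analysis, without arm labels or outcomes where feasible, against a written definition of a major deviation. Say whether {18a} and {21a} describe the same body.

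The cost is wording in the protocol or analysis plan and some preparation of the listings shown to the committee. No data collection or sample size changes, and a deviation-free result remains available as a sensitivity analysis.

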### Adverse event reporting and harms {22}

No risks were identified for patients in this study. The adverse events observed are those usually seen in standard care. The primary outcome is the number of adverse events occurring during AVF puncture: unipuncture failure, bipuncture failure, simple hematoma, hematoma not allowing continuation of dialysis. The coordinating investigator will be informed by the study staff in case of any other adverse events. The coordinating investigator will notify the sponsor by email without delay.

### Frequency and plans for auditing trial conduct {23}

Frequency and procedures for auditing trial conduct, if any, and whether the process will be independent of investigators and the sponsor. No audits of this study are planned.

### Plans for communicating important protocol amendments to relevant parties (e.g., trial participants, ethical committees) {25}

When applicable, the trial steering committee will communicate substantial protocol modifications to relevant parties (People Protection Committee, trial participants and study professionals). The protocol in in the clinical trial registry will be updated.

### Dissemination plans {31a}

The results of the trial will be published in international peer-reviewed scientific journals. Participants, patients, and nurses will also be informed.

## Discussion

AVF puncture in patients undergoing chronic hemodialysis is a procedure that nurses repeat many times. The quality of the procedure determines the success of the treatment and the patient’s comfort. This procedure requires specific skills to avoid multiple complications.

Currently, the technique for puncturing AVF is passed by companionship within hemodialysis departments. Standardization of the procedure is part of a drive to optimize practices and continuously improve care. In this study, we expect to observe a significant reduction in pain intensity for patients, as well as a reduction in the number of hematomas. The reduction in these adverse events will lead to an extension of AVF lifespan, an increase in dialysis quality, and possibly a gain in quality of life for the patient.

The strong point of our study is the use of procedural training, which is innovative in several aspects. It is little used in the continuing education of professionals. It enables the team approach to AVF puncture to be conceptualized and then modeled in procedural simulation. The contribution of therapeutic communication in procedural workshops enables a holistic approach to patient management, despite the technical nature of the treatment. Moreover, the evaluation of the direct benefit of training for the patient (Kirkpatrick level 4) is poorly described in the literature.

This study has several limitations. Firstly, data collection concerning the occurrence of adverse events is declarative in nature. Nurses may underreport/overreport the occurrence of events for fear of being judged. This risk is present in both the data collection and the comfort questionnaire. Then, with regard to distance learning, we cannot be totally sure that it is the nurses who log on, carry out the distance learning, and validate the quizzes.

## Trial status

The protocol version number is V03_30.06.2022. Recruitment began in September 2022, and we expect recruitment to be completed by March 2024.

## Data Availability

The principal coordinating investigator, the monitoring team, and the methodologist will have access to the final dataset. Dataset is under sponsor responsibility, and any data required to support the protocol can be supplied on request directly with the sponsor.

## Abbreviations

CRF: Case report form
NS: Numeric scale
AVF: Arteriovenous fistula
HD: Hemodialysis
TT: Theoretical training group (control group)
TTST: Theoretical training + simulation-based training group (experimental group)
